**Complete blood count (no blood transfusion or G-CSF use within 14 days prior to screening):**

1. Hemoglobin ≥ 90 g/L;
2. Absolute Neutrophil Count (ANC) ≥ 1.5×10^9^ /L;
3. Platelet count ≥ 75 × 10^9^ /L;

**Biochemical tests (no albumin use within 14 days prior to screening):**

1. Albumin ≥ 28 g/L;
2. Total bilirubin ≤ 2 × upper limit of normal (ULN);
3. Aspartate aminotransferase (AST), alanine aminotransferase (ALT) ≤ 5 × ULN;

g) Alkaline Phosphatase (ALP) ≤ 5×ULN;

h) Creatinine ≤ 1.5×ULN;

**Coagulation function:**

1. International normalized ratio (INR) or prothrombin time (PT) ≤1.5×ULN;

J) Activated Partial Thromboplastin Time (APTT) ≤ 1.5×ULN.

## Exclusion criteria

Previous or concurrent diseases:

1. Histologically/cytologically confirmed previous diagnosis of fibrolamellar hepatocellular carcinoma, sarcomatoid hepatocellular carcinoma, cholangiocarcinoma, or other components;
2. History of malignancies other than hepatocellular carcinoma, unless meeting the following criteria:
   1. The patient has undergone potentially curative treatment and has no evidence of the disease for 5 years;
   2. Successfully received resection for basal cell carcinoma of the skin, squamous cell carcinoma of the skin, superficial bladder cancer, cervical carcinoma in situ, and other in situ cancers;
3. Diffuse tumor lesions;
4. Tumor vascular invasion presents one or more of the following conditions:

a) Involvement of the superior mesenteric vein;

b) Involvement of the inferior vena cava;

1. History of hepatic encephalopathy, hepatorenal syndrome, or history of liver transplantation;
2. Clinical symptoms requiring drainage of pleural effusion, ascites, or pericardial effusion;
3. Central nervous system metastasis;
4. History of severe mental illness;
5. Diseases affecting the absorption, distribution, metabolism, or clearance of the study drug (such as severe vomiting, chronic diarrhea, intestinal obstruction, malabsorption, etc.);

Previous or concomitant medications/treatments:

1. Previous receipt of allogeneic stem cell or solid organ transplantation;
2. Previous treatment with targeted therapies against VEGF and/or VEGFR, RAF, MEK signaling pathways such as sorafenib, lenvatinib, regorafenib, or immune modulators such as anti-PD-1, anti-PD-L1, anti-CTLA-4;
3. Patients who have previously received other systemic anti-tumor therapies, including traditional Chinese medicine with anti-tumor indications, within less than 2 weeks prior to the study medication, or those whose adverse events from previous treatments have not recovered to ≤ CTCAE Grade 1; Toxic reactions from prior cancer treatments do not include alopecia and Grade 1/2 neurotoxicity caused by oxaliplatin;
4. Concurrent use of medications that may prolong QTc and/or induce Torsades de Pointes (TdP), or medications that affect drug metabolism;
5. A history of or currently having congenital or acquired immunodeficiency diseases;
6. Active or previously recorded autoimmune diseases or inflammatory diseases (including but not limited to: autoimmune hepatitis, interstitial pneumonia, inflammatory bowel disease, systemic lupus erythematosus, vasculitis, uveitis, pituitary inflammation, hyperthyroidism or hypothyroidism, asthma requiring bronchodilator treatment, etc.), individuals with vitiligo or asthma that has completely resolved in childhood, and those who require no intervention in adulthood may be included;
7. Previous receipt of allogeneic stem cell or solid organ transplantation;
8. Patients who have used systemic immunosuppressive therapy within 2 weeks prior to enrollment, or are expected to require systemic immunosuppressive therapy during the study, except for the following situations:
9. Intranasal, inhaled, topical, or local injection (e.g., intra-articular injection) corticosteroids;
10. Doses not exceeding 10 mg/day of prednisone or other equivalent systemic corticosteroids;
11. Corticosteroids used prophylactically for hypersensitivity reactions;

Safety:

1. Patients with known or suspected allergy to donafenib or similar drugs, or a history of hypersensitivity reactions to chimeric or humanized antibodies or fusion proteins, or those allergic to the excipients of the investigational drug;
2. Active bleeding or coagulation dysfunction, with a tendency to bleed or currently undergoing thrombolysis, anticoagulation, or antiplatelet therapy;
3. History of thrombosis or thromboembolic events within the past 6 months, such as stroke and/or transient ischemic attack, deep vein thrombosis, pulmonary embolism, etc.;
4. History of esophageal or gastric variceal bleeding events due to portal hypertension within the past 6 months, or any life-threatening bleeding events occurring within the past 3 months;
5. Significant clinically meaningful cardiovascular diseases, including but not limited to acute myocardial infarction, severe/uncontrolled angina, or coronary artery bypass surgery within the past 6 months, congestive heart failure (NYHA classification >2), poorly controlled or requiring pacemaker treatment for arrhythmias, and hypertension that is not controlled by medication (systolic blood pressure ≥140 mmHg and/or diastolic blood pressure ≥90 mmHg);
6. Other significant clinical and laboratory abnormalities that the investigator believes affect the safety assessment, such as: uncontrolled diabetes, chronic kidney disease, grade II or higher peripheral neuropathy (CTCAE V5.0), thyroid dysfunction, etc.;
7. Severe infections that are active or poorly controlled clinically; Active infections, including:

a) Positive for human immunodeficiency virus (HIV) (HIV1/2 antibodies);

b) Active hepatitis B (positive HBsAg or HBV DNA > 2000 IU/ml and abnormal liver function);

c) Active hepatitis C (HCV antibody positive or HCV RNA ≥ 10^3^ copies/ml and liver function abnormal);

d) Active tuberculosis;

e) Other uncontrolled active infections (CTCAE V5.0 > grade 2);

1. Not yet recovered from surgery, such as having unhealed incisions or severe postoperative complications;
2. Pregnant or breastfeeding women, as well as female or male patients of childbearing potential who are unwilling or unable to take effective contraceptive measures.

## Criteria for Termination of Study

### Early Termination of the Study

The investigator may terminate this study at any time, with reasons for early termination including but not limited to:

1. The discovery of unexpected, significant, or unacceptable risks to subjects enrolled in the study during the study period;
2. The discovery of significant errors in the clinical research protocol during the study period, making it difficult to evaluate the investigational drug;
3. Request for termination by health/regulatory authorities.

### Early withdrawal of subjects

If a subject withdraws early from the investigational drug treatment, the reasons for withdrawal should be understood and recorded as much as possible. Additionally, arrangements should be made for the subject to undergo all examinations listed in Appendix 1 for the end-of-treatment visit, and to record all adverse events and concomitant medications within 30 days after the last administration or before starting new antitumor therapy (whichever occurs first).

Subjects who withdraw early from investigational drug treatment due to disease progression (with imaging progression meeting both RECIST v1.1 and mRECIST criteria), starting new antitumor therapy, or reasons other than pregnancy will continue to be followed for efficacy until disease progression occurs, new antitumor therapy is initiated, informed consent is withdrawn, loss to follow-up occurs, death, or the study is terminated early (whichever occurs first).

Subjects who discontinue investigational drug treatment due to disease progression (with imaging progression meeting both RECIST v1.1 and mRECIST criteria) or initiation of new antitumor therapy or pregnancy will continue to be followed for survival until the subject withdraws informed consent, is lost to follow-up, dies, or the study is terminated early (whichever occurs first).

If a subject refuses or is unable to return for visits, every effort should be made to contact the patient or an informed contact by phone to determine survival status.

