| **Research Process** | **Screening Period:**  The investigator must fully inform the patient of the potential benefits and risks of this clinical trial. After the patient voluntarily signs the informed consent form, various screening examinations will begin, including the following items:  1) Collect medical history, smoking history, alcohol history, and demographic data  2) Vital signs, physical examination, blood pressure monitoring, ECOG score  3) Adverse events, concomitant medication  4) Laboratory tests   - Complete blood count: including red blood cell count, hemoglobin, hematocrit, white blood cell count and differential (neutrophils, lymphocytes, eosinophils, monocytes, basophils) and platelet count; - Blood biochemistry: including total protein, albumin, globulin, blood glucose, urea/urea nitrogen, creatinine, alkaline phosphatase, lactate dehydrogenase, total bilirubin, direct bilirubin, indirect bilirubin, AST, ALT, γ-glutamyl transferase, calcium, phosphorus, magnesium, potassium, sodium, chloride, amylase, uric acid, creatine kinase, troponin; - Virology tests: Hepatitis B qualitative five items and HBV-DNA, HCV-RNA, HIV; - Tumor markers: AFP; - Thyroid function: TSH, free T3, free T4; - Urinalysis: including specific gravity, pH, urine glucose, protein, casts, ketones, urine red blood cells, urine white blood cells; If there are two consecutive urine protein tests showing ++ or higher, or if the doctor determines the results to be abnormal and clinically significant, a 24-hour urine protein quantification test is required; - Fecal occult blood; - Coagulation function: TT, PT, INR, APTT; - Cardiac ultrasound examination: particularly pay attention to the evaluation of left ventricular ejection function; - 12-lead electrocardiogram (ECG); - Imaging examination: CT or MRI (Note: examinations conducted within 4 weeks prior to screening at the same institution are acceptable); - Women of childbearing age must undergo pregnancy testing to exclude pregnancy;   If all the above screening examination items meet the enrollment criteria for this study, the patient will be enrolled.  **Treatment period:**  After enrollment, subjects will first take oral donafenib tablets for 3 to 7 days. After the investigator assesses that the subjects can tolerate it, the subjects will receive intravenous infusion treatment with sintilimab injection. On the day of sintilimab infusion or the following day, they will begin approximately 1 day of HAIC treatment (the total number of subsequent HAIC treatments will be conducted as needed by the investigator based on the patient's actual condition). Afterwards, subjects will visit every 3 weeks (calculated from the day of the first infusion of sintilimab), with a time window of ±3 days. Every 6 weeks, imaging assessments will evaluate efficacy (using both RECIST v1.1 and mRECIST criteria for tumor assessment), until the subject first shows imaging-confirmed disease progression (meeting both RECIST v1.1 and mRECIST criteria for imaging progression) or intolerable toxicity.  **Follow-up after treatment ends:**  Patients need to undergo safety follow-up and survival follow-up after treatment ends.  In addition, for patients who have not progressed but discontinued treatment due to intolerance, follow-up is required every 12 weeks (within 2 years after the first administration) or every 24 weeks (after 2 years of the first administration) until definitive imaging evidence of progression or death is obtained.  For specific follow-up times and related examination items, please refer to the flowchart. |

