### Survival follow-up

Survival follow-up is required after the investigator determines there is evidence of disease progression or the initiation of new antitumor therapy. Survival follow-up is conducted every 12 weeks, with telephone follow-ups to the subject or their relatives to record the subject's survival status, until the subject withdraws the ICF, is lost to follow-up, dies, or the study is terminated early (whichever occurs first).

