### Overall survival （overall survival, OS ）

The time from the date of enrollment to the date of death from any cause. If the subject is still alive at the database cutoff date, censoring will be performed at the last survival follow-up date in the database.

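### Survival follow-up has three conflicting triggers, and the OS censoring date, read literally, does not exist for living patients without progression or new therapy

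*Protocol*

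**What the plan says.** Four places bear on who is followed for survival, and one on how OS is censored.

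- **Protocol Summary, Research Process.** The rule is unconditional: "Patients need to undergo safety follow-up and survival follow-up after treatment ends". It adds that, "for patients who have not progressed but discontinued treatment due to intolerance, follow-up is required every 12 weeks" up to two years from first dosing and every 24 weeks after that, "until definitive imaging evidence of progression or death is obtained".
- **Section 4.3.3 (early withdrawal of subjects), survival sentence.** Subjects who stop drug for progression "or initiation of new antitumor therapy or pregnancy will continue to be followed for survival until the subject withdraws informed consent". The test is the reason for stopping.
- **Section 4.3.3, efficacy sentence.** Subjects who withdraw early because of progression, "starting new antitumor therapy, or reasons other than pregnancy will continue to be followed for efficacy until disease progression occurs". As written, progression and new therapy are reasons that lead into efficacy follow-up.
- **Section 6.5.3.** "Survival follow-up is required after the investigator determines there is evidence of disease progression or the initiation of new antitumor therapy". The test is an event, and pregnancy is not named. "Survival follow-up is conducted every 12 weeks, with telephone follow-ups to the subject or their relatives".
- **Section 7.4.2.** For a subject alive at the database cutoff, "censoring will be performed at the last survival follow-up date in the database".

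In the flowchart (Attachment 1), the survival status row is marked only in the survival follow-up column. It is blank under treatment, end of treatment, safety follow-up and efficacy follow-up.

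**The concern.** The three triggers do not pick out the same patients. A site following the section on early withdrawal would act differently from one following the summary or section 6.5.3. The efficacy sentence in 4.3.3 adds a second conflict, because sections 6.3 and 6.5.2 end scheduled imaging at progression.

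The censoring rule inherits the problem. It points to a kind of visit that, under 6.5.3 and the flowchart, some living patients never have. These are the patients still alive without progression or new therapy. They tend to have long follow-up, so they matter to the right-hand part of the OS curve. OS is a named secondary endpoint estimated by Kaplan-Meier in 30 patients, so a few censoring times set inconsistently can shift the curve. A contact that was never scheduled may not be recoverable at database lock.

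**Working it through.** No formula applies: the sample size is fixed at 30 without design inputs, and the point concerns routing and a date definition. The check is to run each type of patient through the rules.

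| Patient | Summary | 4.3.3 survival sentence | 6.5.3 |
| --- | --- | --- | --- |
| Stops for progression | Yes | Yes | Yes |
| Stops for new antitumor therapy | Yes | Yes | Yes |
| Stops for pregnancy, not progressed | Yes | Yes | Not named |
| Stops for toxicity, not progressed | Yes | No | Not yet |
| Same patient, later progresses or starts new therapy | Yes | No (not the reason for stopping) | Yes |
| Still on treatment, not progressed | Not yet | No | No |

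**Triggers.** The rules agree only in the first two rows. In the pregnancy row, section 6.5.2 halts all tumor assessments, so the progression trigger in 6.5.3 may never be met. Only 4.3.3 and the summary keep that patient in survival follow-up. In the toxicity rows, 4.3.3 taken alone never reaches survival follow-up, whereas 6.5.3 does once progression or new therapy occurs.

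**Efficacy sentence.** Section 4.3.3 sends patients who stopped for progression or new therapy to efficacy follow-up. Section 6.5.2 restricts that follow-up to patients with neither, and section 6.3 ends CT/MRI once progression is confirmed. The survival sentence that follows in 4.3.3 lists progression, new therapy and pregnancy as the survival route. The efficacy route was therefore presumably meant to be every other reason.

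**Censoring date.** Section 7.4.2 needs a survival follow-up date. Under 6.5.3 and the flowchart, two groups of living patients have none: those on treatment without progression, and those in efficacy follow-up. Adopting the summary's trigger would repair the second group only. A patient still on treatment at the cutoff would still have no such date, so 7.4.2 needs its own change.

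**Contact that does exist.** On treatment, visits are every 3 weeks. In efficacy follow-up they are every 12 weeks to year 2 and every 24 weeks after that, against every 12 weeks in survival follow-up. Planned contact in efficacy follow-up is therefore the same up to year 2 and half as frequent after it (24 / 12 = 2). Dated evidence that these patients are alive will exist, but the censoring rule does not refer to it.

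**The case against.** The strongest reply is that this is a matter of wording. Section 6.5.3 is the operative survival follow-up section, and 4.3.3 can be read as saying who goes straight to survival follow-up, without excluding anyone later. A patient who stops for toxicity enters efficacy follow-up under 6.5.2. That follow-up ends at progression, new therapy or death among other events, with the reason recorded in the CRF, and progression or new therapy then starts survival follow-up. Section 4.3.3 also asks for telephone contact on survival status when a subject refuses or cannot attend. The faulty efficacy sentence has little practical effect, since efficacy follow-up would end at once for someone who has already progressed. The last survival follow-up date may simply mean the last contact at which the subject was known alive, and deriving it in detail is normal work for a statistical analysis plan.

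Most of this stands. A reader might infer that OS follow-up is lost after toxicity and that OS censoring is therefore informative. The documents do not support that: 6.5.2 followed by 6.5.3 keeps these patients under observation, and the lapse needs 4.3.3 to be applied alone.

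A reader might also attach a count by borrowing the 10.5-month median PFS and 11.2-month median follow-up of the lenvatinib, toripalimab and HAIC trial in section 1.5. With exponential PFS, 0.5^(11.2/10.5) = 0.48, about 14 of 30 progression-free. That is a different regimen and another study's follow-up time. It places all 30 patients at one common time and includes progression-free patients who started new therapy, whom 6.5.3 does cover. The protocol gives no rate of stopping for toxicity with this combination either.

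The reply does not remove the conflict between the three triggers, the error in the efficacy sentence, or the fact that 7.4.2 fixes a date tied by name to a visit type that some living patients do not have. That date is stated in the protocol and has not been left open for the analysis plan.

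**Conclusion.** The point holds as a contradiction to reconcile and a censoring rule that fails when applied literally. The three triggers differ for patients who stop for toxicity and for those who stop for pregnancy. The efficacy sentence in 4.3.3 conflicts with 6.3 and 6.5.2. The OS censoring date is undefined for patients alive without progression or new therapy, unless the phrase is taken to mean the last date known alive.

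No number of affected patients can be derived from the protocol. The consequence is limited to OS, a descriptive secondary endpoint in an exploratory 30-patient trial. The primary objective response rate does not depend on any of these passages. The change is still worth making, because it costs little and a missed contact may not be recoverable later.

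**What to change.** 1. Reconcile sections 4.3.3 and 6.5.3 with the Protocol Summary: vital status is followed after the end of treatment for every subject, whatever the reason for stopping. Efficacy visits may serve as the contact while they continue.
2. Correct the efficacy sentence in 4.3.3 so that it applies to reasons other than disease progression, new antitumor therapy or pregnancy.
3. In the flowchart, mark survival status at the end-of-treatment, safety follow-up and efficacy follow-up visits.
4. In section 7.4.2, censor OS at the last date the subject is known to be alive from any contact. This also covers patients still on treatment at the cutoff.

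The cost is amendment wording, a few extra flowchart entries and possibly some telephone calls, which the summary already implies.

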## Exclusion Criteria

Before statistical analysis of the data, the principal investigator and the statistical unit will determine whether individual cases should be excluded. In the event of any of the following situations, the principal investigator should comprehensively assess whether to exclude the subject based on the extent of the subject's completion of the study and the reasons for early withdrawal, and provide relevant explanations. The CRF form should be retained for reference.

1. The subject violated important inclusion/exclusion criteria;
2. During the study period, the subject did not comply with the study protocol, such as not using the investigational drug, being unable to collect safety evaluation samples as required by the study protocol, or having no data at all;
3. During the study period, the investigator believes that the subject has other factors that prevent continued participation in the study, such as the concurrent use of other antitumor therapies during the study period, and actually terminates the subject's participation in the study.

# Investigational Drug

## Investigational Drug Information

**Donafenib tablets:**

Dosage form: Tablet

Specification: 100 mg/tablet

Ingredients: 4-(4-{3-[4-chloro-3-(trifluoromethyl)phenyl]-ureido}-phenoxy)-2-(N-1′,1′,1′-trideuteromethyl)pyridine-3-carboxamide salt

Storage conditions: Store sealed below 25°C

Shelf life: 36 months

Manufacturer: Suzhou Zelgen Biopharmaceutical Co., Ltd.

**Sintilimab injection:**

Dosage form: Injection

Specification: 10 ml: 100 mg, 1 vial/box

Component: Humanized anti-PD-1 monoclonal antibody

Storage conditions: Store and transport protected from light at 2-8℃

Shelf life: 24 months

Manufacturer: Innovent Biologics (Suzhou) Co., Ltd.

The preparation of the drugs used in the study complies with the requirements of the 'Good Manufacturing Practice for Pharmaceuticals'. The quality meets the standards for clinical research drugs.

## Treatment regimen

**Donafenib tablets:**

Subjects will start taking donafenib 3-7 days prior to receiving HAIC treatment, with a starting dose of 200 mg, twice daily (200 mg bid). Subjects will take the medication orally twice a day on each administration day, in the morning and evening, on an empty stomach (1 hour before meals or more than 2 hours after meals), with a 12±1 hour interval between doses, and continue taking it.

- - Bid administration on each dosing day, fasting in the morning and evening (1 hour before meals or 2 hours after meals), taken orally once, with an interval of approximately 12 hours between the two doses. Qd administration (occurring during dose adjustment), taken orally once in the morning on each dosing day while fasting (1 hour before meals or 2 hours after meals). It is acceptable for the medication to be taken within 1 hour before or after the scheduled dosing time.
  - If the subject vomits after taking the medication and expels the original drug or part of it, in principle, the medication should not be supplemented, and it should be recorded as a missed dose.
  - If the medication has not been taken 1 hour after the scheduled dosing time, there is no need to supplement the medication, and it should be recorded as a missed dose.
  - donafenib will be administered continuously until the subjects meet the criteria for study termination.

